### Sample size

The statistical software Statmate version 2 (GraphPad Software, Inc., CA, USA) was used to calculate the sample size using the primary outcome variables, the NRS scores for pain and the reduced WOMAC index for function, with a power of 80 % and a significance level of 0.05. The unpublished pilot data on the effects of retro-walking on these variables was used to calculate SD’s. We assume a clinically important difference between two intervention groups of 1.08 in NRS score (*SD* = 1.19) and 4.47 points in functional score assessed using the reduced WOMAC index (*SD* = 4.9). The sample size calculation resulted in 20 participants in each group, or 60 total participants. To allow for a potential follow-up loss of 15 %, we will recruit a minimum of 69 participants.

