### Randomization, allocation concealment, and blinding

The participants who fulfil the inclusion criteria will be randomly assigned to one of three groups (A, B, and C). Blank folders will be numbered from 1 to 69 and will be given concealed codes for the group assignment by an independent researcher and kept in a safe locker. When a participant is eligible and give their consent to participate, an independent therapist will draw the next folder from the file, which will determine the group assignment. A trained research assistant blinded to group assignment will record all measurements.

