### Statistical analysis

Demographic data and baseline scores of all outcome measures will be presented to evaluate baseline comparability of treatment groups. Descriptive data will be reported for each group as the mean change in the outcome measures at baseline and at the end of the trial. Data normality will be tested. Paired t-tests and one-way ANOVA with Bonferroni adjustment for multiple comparisons will be applied to compare within and between group differences of all outcomes (interval/ratio data). The Wilcoxon signed-rank test and Friedman test will be used to compare within and between group differences of all outcome measures (nominal/ordinal data). The probability level for all tests will be set at 0.05 to indicate significance. The intention-to-treat principles will be used for analysis. For missing data, the last observation carried forward method will be used. All data will be analyzed using SPSS software version 22 (SPSS, Chicago, Illinois).

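### The 80% power is calculated at an unadjusted two-group level of 0.05, but the planned pairwise comparisons are Bonferroni-adjusted; with three pairs, power is about 64–66% at 20 per group and 72–74% at 23

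*Protocol article*

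**What the plan says.** The Sample size section works from the two primary variables, "with a power of 80 % and a significance level of 0.05". The effect is a contrast of two groups. For function it is "4.47 points in functional score assessed using the reduced WOMAC index", where the SD is taken as 4.9. For pain the section names a "clinically important difference between two intervention groups of 1.08 in NRS score", where the SD is taken as 1.19. The result is given as: "The sample size calculation resulted in 20 participants in each group, or 60 total participants". An allowance for loss follows: "To allow for a potential follow-up loss of 15 %, we will recruit a minimum of 69 participants", which is 23 per group if the split is equal. The section mentions no adjustment for multiple comparisons.

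For interval or ratio data, the Statistical analysis section says: "Paired t-tests and one-way ANOVA with Bonferroni adjustment for multiple comparisons will be applied". It sets 0.05 as the level for all tests, and specifies intention-to-treat analysis with last observation carried forward (LOCF). It does not say how many comparisons the Bonferroni adjustment covers.

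The third hypothesis in the Hypotheses section is that retro-walking does better than forward-walking, which is a pairwise question.

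**The concern.** A power statement belongs to one test at one significance level. Here the sample size rests on a single two-group comparison at 0.05, while the same difference will be judged after a Bonferroni adjustment, so at a stricter level. The 80% therefore does not describe the planned pairwise test.

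What is at stake is how a non-significant retro-versus-forward result is read. A reader relying on the stated figure would put the chance of missing the clinically important difference at one in five. With 20 per group and three comparisons it is closer to one in three; with 23 per group it is a little over one in four. Estimates are not biased and the type I error is not inflated. The fault is an inconsistency between the sizing level and the analysis level.

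**Working it through.** **Inputs (Sample size section).** NRS: difference 1.08, SD 1.19, so d = 1.08/1.19 = 0.908. Reduced WOMAC: difference 4.47, SD 4.9, so d = 4.47/4.9 = 0.912. There are 20 per group (60 in total), and 69 recruited, or 69/3 = 23 per group.

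**Assumptions.** Tests are two-sided (the protocol does not say; a one-sided calculation gives 16 and 15 per group, so it does not reproduce the plan). Allocation is equal. The Bonferroni divisor is 3, the number of pairs among three groups; other divisors are shown below.

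**Formula.** Power = P(|T| > c). T is noncentral t with noncentrality d·√(n/2), and c is the two-sided critical value at the level used. Degrees of freedom are 2n − 2 for a plain two-sample t-test (38 at n = 20) or 3n − 3 with the ANOVA pooled error (57 at n = 20).

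**Step 1: reproduce the plan's figure.** At n = 20 the noncentrality is 0.908 × √10 = 2.87 (NRS) and 0.912 × √10 = 2.88 (WOMAC). At 0.05 with 38 df, c = 2.02 and power is 79.9% and 80.3%. The stated 20 per group is therefore what an unadjusted two-sided 0.05 gives.

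**Step 2: apply the adjustment.** At 0.05/3 = 0.0167, c rises to 2.50 (38 df) or 2.47 (57 df). Power becomes 64.3% (NRS) and 64.9% (WOMAC) with 38 df, or 65.7% and 66.2% with 57 df. The normal approximation gives 68–69%.

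**Step 3: vary the divisor and the number analysed.** Ranges cover both outcomes and both choices of degrees of freedom.

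| Comparisons covered | Level per test | Power, 20 per group | Power, 23 per group |
|---|---|---|---|
| 1 (as sized) | 0.05 | 80–81% | 85–86% |
| 2 | 0.025 | 70–72% | 77–79% |
| 3 (all pairs) | 0.0167 | 64–66% | 72–74% |
| 6 (all pairs, both primary outcomes) | 0.0083 | 54–56% | 62–65% |

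The 23-per-group column assumes that values filled in by LOCF do not dilute the difference.

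**Step 4: what 20 per group can detect.** For 80% power at 0.0167, d must be 1.064 (38 df) or 1.050 (57 df). In NRS points that is 1.064 × 1.19 = 1.27 or 1.050 × 1.19 = 1.25. In WOMAC points it is 1.064 × 4.9 = 5.21 or 1.050 × 4.9 = 5.14. For the differences as stated, 80% power at 0.0167 would need 27 per group, or 81 evaluable.

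**Step 5: the omnibus F test at 0.05, 20 per group.** Power is about 83–84% if one group alone differs by the assumed amount, and about 71% if the third mean lies midway between the other two.

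**Step 6: an alternative procedure.** This is the F test at 0.05, followed by unadjusted pairwise tests only if F is significant (simulated, pooled error, 20 per group). Power for the assumed pairwise difference is about 70% with the third mean midway, 76–77% with it equal to one of the pair, and 80–81% with it well outside them. Bonferroni alone gives 66%.

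**The case against.** The strongest objection is that the divisor is not in the protocol, so a flat statement that the true power is 65% goes further than the text. That stands. Three is the natural count for three groups, but it is an assumption, and the figure has to be given with its range. The range does not rescue the stated power: even two comparisons leave 70–72% at 20 per group and 77–79% at 23.

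Second, under intention-to-treat with LOCF the analysed number may be nearer 23 than 20 per group. This also stands, so both figures belong in the statement. The higher one is not assured, because a baseline value carried forward tends to shrink a treatment difference.

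Third, the NRS and a five-point Likert WOMAC might be treated as ordinal. The Statistical analysis section gives ordinal data to rank-based tests, in a sentence that names no adjustment. The branch is real, but it does not save the 80%: the calculation was done on means and SDs, and so corresponds to the t-test and ANOVA branch.

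Fourth, the omnibus F test is planned at 0.05 and reaches about 83% in one configuration. That is correct, and a reader might wrongly infer that every planned test falls short. The point is limited to the pairwise tests, which are what the Sample size section targets and what the third hypothesis needs.

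**Conclusion.** The point holds as an inconsistency between the level used for sizing and the level used for analysis. The stated 80% is not the power of the planned Bonferroni-adjusted pairwise test under any divisor of two or more, whether 20 or 23 per group are analysed. With three comparisons it is about 64–66% at 20 per group and 72–74% at 23. This rests on two-sided tests, equal allocation, the protocol's own differences and SDs and, for the second figure, LOCF not diluting the effect.

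Two stronger readings are tempting. One is that the sample size arithmetic is wrong. It is not: it reproduces at the level stated. The other is that the trial must be enlarged. Nothing in the protocol requires that; what needs correcting is the claim made for the number chosen.

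**What to change.** In the Statistical analysis section, state how many comparisons the Bonferroni adjustment covers and whether it spans both primary outcomes. In the Sample size section, restate the power to match. With three pairwise comparisons: about 65% at 20 completers per group (72–74% if 23 per group are analysed) for differences of 1.08 NRS and 4.47 WOMAC points. Equivalently, 20 per group give 80% power for about 1.25–1.27 NRS and 5.1–5.2 WOMAC points. If another count is chosen, use the corresponding row of the table. The cost is one restated figure and one sentence, a less favourable power statement, and no extra participants.

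Optionally, replace Bonferroni with the F test at 0.05 followed by unadjusted pairwise tests only when F is significant. With exactly three groups this holds the family-wise error at 5% within each outcome, and raises pairwise power to roughly 70–81% depending on the third group's mean. It is a design choice, since Bonferroni is itself valid, and it does not guarantee 80%. If adopted, it should be fixed before outcome data are seen.

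### The 80% power holds for one unadjusted two-group test at 0.05; under the planned Bonferroni-adjusted comparisons of three arms, 20 per group gives about 66%

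*Protocol article*

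**What the plan says.** All sizing statements are in the protocol article, Sample size. The calculation was made "with a power of 80 % and a significance level of 0.05". The target is a single two-group difference: "We assume a clinically important difference between two intervention groups of 1.08 in NRS score", with an SD of 1.19, and "4.47 points in functional score assessed using the reduced WOMAC index (*SD* = 4.9"). The result is given as "The sample size calculation resulted in 20 participants in each group, or 60 total participants". The allowance for loss follows: "To allow for a potential follow-up loss of 15 %, we will recruit a minimum of 69 participants". The section mentions no adjustment of the significance level.

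The section Statistical analysis fixes the between-group test for interval and ratio data: "one-way ANOVA with Bonferroni adjustment for multiple comparisons will be applied". It sets 0.05 for all tests and plans an intention-to-treat analysis with last observation carried forward. There are three groups (Randomization, allocation concealment, and blinding). The third entry under Hypotheses is that retro-walking does better than forward-walking, which is a pairwise contrast between two of the three arms.

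**The concern.** The sample size and the analysis use different significance levels. The sizing treats the trial as one two-group comparison at 0.05. The analysis spends that 0.05 over the pairwise comparisons of three arms, so each comparison faces a stricter threshold. The retro- versus forward-walking hypothesis is answered by one of these adjusted comparisons, so their power is the power that matters for it.

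If the gap is material, the protocol promises a power its own analysis does not have. A non-significant retro- versus forward-walking result would then be weaker evidence against a difference than a reader relying on 80% would suppose. The point concerns the stated power only; it is not an argument for or against Bonferroni.

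**Working it through.** **Inputs** (protocol article, Sample size, unless noted)
- NRS pain: difference 1.08, SD 1.19, so d = 1.08/1.19 = 0.908.
- Reduced WOMAC function: difference 4.47, SD 4.9, so d = 4.47/4.9 = 0.912.
- n = 20 per group; 69 recruited, so 69/3 = 23 per group if allocation is equal.
- Stated level 0.05 and power 80%. Sidedness is not stated.
- Three arms, hence three pairwise contrasts; Bonferroni adjustment (Statistical analysis). The number of contrasts is not stated; three is an assumption, varied below.

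**Formula.** Two-sided power for one contrast = P(|T| > c), where T is noncentral t with noncentrality d·√(n/2), and c is the 1 − α/2 quantile of the central t. The degrees of freedom are 2n − 2 = 38 for a stand-alone two-group test, or 3n − 3 = 57 with the pooled ANOVA error.

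**Step 1: reproduce the plan's figure.** At n = 20 the noncentrality is 0.908 × √10 = 2.87 for NRS and 0.912 × √10 = 2.88 for WOMAC. With α = 0.05 and 38 df, c = 2.024.
- NRS power: 79.9%.
- WOMAC power: 80.3%.

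The normal approximation needs 20 (NRS) and 19 (WOMAC) per group; the t calculation needs 21 and 20. A one-sided 0.05 test would need only 16 and 15 (normal approximation). The stated 20 is therefore a two-sided, unadjusted calculation for one two-group contrast.

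**Step 2: use the level of the planned comparisons.** α = 0.05/3 = 0.0167. With 57 df, c rises to 2.467; the noncentrality is unchanged.

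| Power at n = 20, α = 0.0167 | NRS | WOMAC function |
|---|---|---|
| t, pooled error, 57 df | 65.7% | 66.2% |
| t, two-group error, 38 df | 64.3% | 64.9% |
| Normal approximation | 68.3% | 68.8% |

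**Step 3: what 80% power would correspond to.** At n = 20, α = 0.0167 and 57 df, the detectable d is 1.050. That is 1.050 × 1.19 = 1.25 NRS points and 1.050 × 4.9 = 5.14 WOMAC points. Conversely, the differences the protocol assumed would need 27 per group by the t calculation.

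**Step 4: vary the assumptions** (t-test power; each range covers both outcomes and both choices of df).

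| Contrasts adjusted | 20 per group | 23 per group (all 69 analysed) |
|---|---|---|
| Three (0.0167) | 64–66% | 72–74% |
| Two (0.025) | 70–72% | 77–79% |

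If the adjustment also covered the two primary outcomes used for sizing (six tests, 0.0083), power at 20 per group would be 54–56%.

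**The case against.** The strongest reply is that nothing in the Sample size section is miscalculated. It claims 80% at 0.05 for a two-group difference, and that reproduces. The section does not say that the 80% applies to each adjusted contrast. The fault is therefore a mismatch between two sections, not a slip in a formula. That description is fair, but it does not rescue the figure: a power statement is read as describing the planned analysis, and here it does not.

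Second, three contrasts is an inference. The Statistical analysis section does not count the comparisons, and the first two hypotheses name no comparator, so within-group tests might be meant for them. This stands as a caveat. All pairs is the ordinary meaning of Bonferroni after a three-group ANOVA, and two contrasts still give only 70–72%.

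Third, under intention-to-treat with carried-forward values all 69 may be analysed, giving 23 per group and 72–74%. This also stands in part, although carried-forward values may dilute the effect and the protocol ties its 80% to 20 per group. Taking both concessions together gives 77–79% by t. Only the normal approximation then reaches 80%, and only for WOMAC (80.3%; NRS 79.9%).

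Fourth, the SDs come from unpublished pilot data. An SD 10% smaller (an illustrative assumption) would give 76% for NRS at 20 per group and 83% at 23, at the adjusted level. A larger SD would cut power in the same way. This is uncertainty about an input; it does not reconcile the two significance levels.

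Finally, the overall F test at 0.05 has 71–84% power at 20 per group, depending on how the three means lie, but it does not answer whether retro-walking beats forward-walking. The adjusted tests remain valid: type I error is not inflated.

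**Conclusion.** The concern holds. On the protocol's own differences and SDs, 20 per group gives 80% power only for one unadjusted two-group test. For a Bonferroni-adjusted pairwise contrast among three arms it gives about 66% (64–69% across the t and normal calculations), a shortfall of about 14 percentage points. The chance of missing the assumed difference is about 34%, not 20%.

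This rests on three adjusted contrasts, equal SDs across the groups, adjustment over contrasts but not over outcomes, and 20 evaluable participants per group. Relaxing the number of contrasts, the analysed number, or both moves t-test power within 64–79%, below 80% throughout.

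**What to change.** In the Sample size section, state which pairwise contrasts are adjusted and the level for each, and give the power on that basis. For all three pairs the text could read: with 20 evaluable participants per group, each Bonferroni-adjusted pairwise contrast (two-sided 0.0167) has about 66% power for 1.08 NRS points or 4.47 reduced WOMAC function points; 80% power is reached at about 1.25 and 5.1 points. If a different set of contrasts or another multiplicity procedure is chosen, restate the figure for that choice.

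The cost is a few sentences and a less favourable stated power. Enrolment and conduct need not change.

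### A recruitment target of 69 covers a follow-up loss of about 13%, not the stated 15%; the shortfall is small and concerns observed week-6 completers

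*Protocol article*

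**What the plan says.** The Sample size section of the protocol article gives the planning values for the two primary outcomes: a "difference between two intervention groups of 1.08 in NRS score" with an SD of 1.19, and "4.47 points in functional score assessed using the reduced WOMAC index" with an SD of 4.9. The calculation was run "with a power of 80 % and a significance level of 0.05". Its result is stated as "The sample size calculation resulted in 20 participants in each group, or 60 total participants". The next sentence adds the allowance for loss: "To allow for a potential follow-up loss of 15 %, we will recruit a minimum of 69 participants".

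The same number appears elsewhere. The Methods/Design paragraph of the abstract and the Participants section both give sixty-nine participants. The section on randomization, allocation concealment, and blinding says "Blank folders will be numbered from 1 to 69", for patients "randomly assigned to one of three groups (A, B, and C").

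The Statistical analysis section plans an intention-to-treat analysis and adds: "For missing data, the last observation carried forward method will be used". According to the Outcome measures section, outcomes are measured only at baseline and at week 6.

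**The concern.** Follow-up loss occurs among the people recruited. An allowance of 15% therefore has to be set so that 85% of the recruited number is at least the number required. The sentence implies that 69 recruits less 15% leave the required 60, and they do not.

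What is at stake is whether the sample-size statement is true as published. The base figure of 20 per group has almost no slack: it sits at 80% power for both primary outcomes. Even a small shortfall in completers therefore takes the pairwise power slightly below the stated target, and any reader can see the mismatch in one line of arithmetic.

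**Working it through.** **Inputs, all from the Sample size section unless noted**
- NRS pain: difference 1.08, SD 1.19, so standardised difference 1.08/1.19 = 0.908.
- Reduced WOMAC function: difference 4.47, SD 4.9, so 4.47/4.9 = 0.912.
- Significance level 0.05, power 80%. Sidedness is not stated; two-sided is assumed here.
- Required before loss: 20 per group, 60 in total.
- Allowance for loss: 15%. Recruitment target: 69.
- Three arms (randomization section). Equal allocation is assumed, as the figure of 20 in each group implies.

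**Step 1. Reproduce the base figure.** The two-sample t-test at two-sided 0.05 and 80% power requires 20.07 per group for NRS pain and 19.87 per group for WOMAC function. Both agree with the stated 20 per group and 60 in total.

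**Step 2. Reproduce the recruitment target.** Required number × (1 + loss) = 60 × 1.15 = 69.0, an exact match with the stated 69.

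**Step 3. Check what 69 delivers.**
- Completers at 15% loss: 69 × (1 − 0.15) = 58.65.
- Per group: 58.65/3 = 19.55.
- Largest loss that still leaves 60: (69 − 60)/69 = 9/69 = 13.0%.

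**Step 4. Number needed for a 15% loss.** Required number ÷ (1 − loss):
- In total: 60/0.85 = 70.6, so 71. Check: 71 × 0.85 = 60.35.
- By arm: 20/0.85 = 23.5, so 24 per arm and 72 in total. Check: 72 × 0.85 = 61.2.

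The gap is therefore 2 participants (71 − 69), or 3 with equal arms (72 − 69).

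**Step 5. Effect on power** (two-sample t-test, two-sided 0.05, a single comparison between two groups):

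| Completers per group | NRS pain | WOMAC function |
|---|---|---|
| 20 | 79.9% | 80.3% |
| 19.55 | 78.9% | 79.3% |
| 19 | 77.7% | 78.1% |

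The expected shortfall from 20 to 19.55 costs one percentage point for each outcome.

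**The case against.** Several counter-arguments have weight.

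- **Everyone randomised is analysed.** This stands. With intention to treat and last observation carried forward, a participant who misses week 6 enters with the baseline value, so the nominal number analysed could be all 69, about 23 per group. A reader might infer that fewer than 20 per group would be analysed; the Statistical analysis section does not support that. What falls short is the number with an observed week-6 outcome, which is what an allowance for follow-up loss is meant to protect. A carried-forward baseline records zero change and does not replace an observed outcome.
- **The effect is negligible.** Largely true. If the error variance is pooled over all three groups, as in the planned one-way ANOVA, power at 19.55 per group is 79.6% for NRS pain and 80.0% for WOMAC function, so the target is practically met. The 15% is also only a potential loss with no source given, and in whole participants the difference is between losing 3 of 23 (13.0%) and 4 of 23 (17.4%).
- **The target is called a minimum.** This stands in part. A reader might infer from the 69 folders that recruitment cannot go higher. The article does not say that folders may not be added. It does, however, use 69 as its working number in the abstract, the Participants section and the randomization section, so the word gives little cover.
- **No inflation formula is printed.** Correct. That 60 was multiplied by 1.15 is inferred from the exact match. The conclusion does not depend on it, because 69 fails to leave 60 after a 15% loss however it was obtained.

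A reader might also be tempted to join this to the Bonferroni adjustment in the Statistical analysis section and present the two as one serious loss of power. That would misattribute it: any loss from a stricter significance level comes almost entirely from that level and is present at the full 20 per group. It is a separate question.

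**Conclusion.** The point holds as a small arithmetic error in a stated property of the design. With 69 recruited, a 15% loss leaves an expected 58.65 completers and not 60; the target covers a loss of 13.0%. The shortfall is 2 participants, or 3 with equal arms, and costs about one percentage point of power for each primary outcome.

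The power figures rest on two-sided testing, equal allocation, loss spread evenly over the arms, the planning differences and SDs as given, and a single pairwise comparison at 0.05 among completers. The recruitment arithmetic in steps 3 and 4 needs none of the assumptions about testing or effect size.

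The documents do not support reading this as a materially underpowered trial, as a deficit in the number analysed, or as a reason on its own to enlarge the trial. It is a correction of wording at the lowest level of importance.

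**What to change.** Reword the last sentence of the Sample size section in one of two ways:

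- 69 participants (23 per group) allow for a follow-up loss of about 13%; or
- with 69 participants, a 15% loss would leave about 59 with week-6 data (19 to 20 per group), giving power of about 79% for a single two-sided comparison at 0.05.

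Either version costs one sentence and leaves recruitment, the folders and the other mentions of 69 unchanged. If the sponsor would rather keep the 15% allowance with 20 completers in every arm, the consistent number is 72 (24 per arm), with folders numbered to 72 and sixty-nine changed in the abstract and the Participants section. That means three more participants, and a gain of about one percentage point of power does not require it.
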